### Patient and Public Involvement

The protocol of this study was discussed and developed by a multidisciplinary team of experts including epidemiologists, clinicians, and statisticians; however, no patients or public people were involved in the design phase.

### Primary Endpoints

The primary endpoint is a composite of death from any cause and major adverse cardiac and cerebrovascular events (a composite of a recurrence of Takotsubo syndrome, myocardial infarction, stroke or transient ischemic attack, or death from any cause) evaluated during the in-hospital period and at the 1- and 6-month follow-up.

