### Intervention and Follow-Up

All eligible patients in the RIC and control groups will receive routine monitoring and medical treatment. Moreover, the patients in the RIC group will receive RIC treatment through an electric auto-control device that has been delineated by Ji et al. (patent number ZL200820123637.X, China): (43) a blood pressure cuff will be placed around the upper arm of the patient and inflated to a pressure of 200 mmHg (44) for 5 min and then deflated for reperfusion for 5 min. The inflation and deflation will be performed for four cycles each time, three times a day for a total of five consecutive days. If an upper limb is affected by the stroke, the other normal upper limb will be selected for RIC treatment. Blood samples will be collected before RIC treatment, every 48 h after RIC treatment until discharge from the NICU. The patients in the control group will not receive RIC treatment; however, blood samples will be collected at the same time points as those in the RIC group. Blood samples will be used for the detection of the following biomarkers: cardiac troponin I (cTnI), N-terminal pro B-type natriuretic peptide (NT-pro BNP), high-sensitivity C-reactive protein (HS-CRP), interleukin-6 (IL-6), interleukin-10 (IL-10), interleukin-17 (IL-17), plasminogen activator inhibitor-1, plasma tissue plasminogen activator, micro-RNA-126, micro-RNA-155, serum nitric oxide (NO), blood uric acid, white blood cell count, and platelet aggregation rate. The electrocardiograph and echocardiography will be performed simultaneously every 48 h after RIC treatment until discharge from the NICU to evaluate the cardiac indicators such as ECG ST segment, percent of arrhythmia, ejection fraction, and left ventricular end-diastolic diameter (LVEDD). All eligible patients will be followed up by core team members based on clinical visits, medical records, or telephone interviews at 1 and 6 months after discharge and undergo the aforementioned examinations and serological tests (Table 1).

**Table 1 T1:** Data collection timeline.

	**Cardiac examination (electrocardiograph, echocardiography)**	**Blood samples**	**Patients' characteristics (mRS or GOS)**	**Clinical outcomes**
At admission	✓	✓	✓	
Before RIC	✓	✓		
Every 48 h after RIC	✓	✓		
At discharge from NICU	✓	✓	✓	✓
At 1 month after discharge	✓	✓	✓	✓
At 6 months after discharge	✓	✓	✓	✓

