### Secondary Endpoints

The secondary endpoints are death from any cause, a composite of major adverse cardiac and cerebrovascular events, serum cardiac biomarker cTnI, NT-pro BNP, modified Rankin Scale (mRS) score, Glasgow Outcome Score (GOS), cardiac function determined by echocardiography, ECG changes (QT interval and possible ST elevation), and blood uric acid level measured prior to RIC treatment, at discharge from the NICU, and at the 1- and 6-month follow-up. The average hospitalization duration will be recorded as a secondary endpoint to evaluate the efficiency of RIC.

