### Sample Size

No previous studies have focused on utilizing RIC to prevent TTS in patients after acute stroke. Most existing evidence utilized troponin I assay for the detection of cardiac injury. Power calculations for this proof-of-concept study will be based on serial troponin measurements, taken as continuous outcome variables with a predicted difference. Previous studies on RIC indicated a cardioprotective effect of RIC in reducing troponin levels by 18–62% (45–48). Based on the results of a pilot study in our center (the troponin level decreased by 40%, *n* = 10), we hypothesized a troponin level reduction of 37% with 80% power at the 5% significance level, and we calculated a sample size of 60 patients (*n* = 30 in each arm of the study).

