### Data Management and Statistical Analysis

An electronic database will be established to collect the data. Unique numeric identifiers will be assigned to each patient, which will be included in the study database; any other information related to the patient's identity will be excluded. Patients' identification will be solely used for follow-up purposes. Data safety will be supervised by an independent monitoring committee. Descriptive and summary statistics will be calculated for each treatment group for baseline characteristics. Continuous data will be expressed as means (standard deviations) or medians (interquartile ranges) for non-normal continuous data and ordinal data. Primary and secondary endpoints will be analyzed by the intent-to-treat principle. In univariate analyses, patient- and clinical-related factors will be compared *via* the chi-square, analysis of variance, Student's *t*-test, or Mann–Whitney *U* test, when appropriate, between two groups. The variables in the initial model included age, gender, diabetes status, hypertension, smoking status, serum cardiac biomarkers, blood uric acid, ejection fraction, LVEDD, mRS, and GOS at baseline. The relative prognostic significance of the variables in predicting the primary endpoint, mRS and GOS will be assessed by multivariate Cox regression models. Variables associated with a *p* < 0.10 on univariable analysis were included in the multivariable analysis. Kaplan–Meier plots and log-rank tests will be utilized to compare the mRS and GOS between two groups. A *p* < 0.05 will indicate statistical significance. SPSS 13.0 software (SPSS Inc., Chicago, IL) will be used for all statistical analyses.

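### No reading or single analysis of the primary composite is named as primary, and the 1- and 6-month readings are timed from discharge, which treatment may affect

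*Protocol article*

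**What the plan says.** Under Primary Endpoints, the protocol article defines one composite, "evaluated during the in-hospital period and at the 1- and 6-month follow-up". The abstract repeats the three times, and Table 1 collects clinical outcomes at NICU discharge and at both later visits. None is named as primary, and nothing says how the three combine.

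Under Intervention and Follow-Up, patients are seen "at 1 and 6 months after discharge". Table 1 uses the same origin for its last two rows ("At 6 months after discharge" is the final one). Under Secondary Endpoints, stay is an outcome: "The average hospitalization duration will be recorded as a secondary endpoint to evaluate the efficiency of RIC".

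Data Management and Statistical Analysis does not settle the matter. It gives one general threshold ("0.05 will indicate statistical significance"). Its Cox model for the primary endpoint is described as prognostic, and treatment is not among the variables listed. Kaplan-Meier plots and log-rank tests are assigned to mRS and GOS. The chi-square test is listed for comparing patient and clinical factors and is tied neither to the composite nor to a time.

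**The concern.** Two things are at stake.

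First, a composite read at three times, with no reading designated, lets the deciding analysis be chosen after the data are seen. If any one significant reading may count, the trial has up to three chances of a positive result.

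Second, the end of the in-hospital period and the dates of both later visits depend on an event after randomisation. If stay differs by arm, so does the time during which events can be counted. A shorter stay lowers the in-hospital count even when the event rate per day is unchanged. mRS and GOS would also be scored at different stages of recovery. Controls receive no RIC, no sham is described, and the blinding described covers data collection and analysis, so discharge decisions are not stated to be blinded.

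**Working it through.** **Inputs from the protocol article:** 60 patients, 1:1, so 30 per arm; 5% significance level (two-sided assumed, as sidedness is not stated); three assessment periods; visits counted from discharge. **Assumed, because the article gives none:** event rates and lengths of stay.

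**The plan's own figure.** The article states no error rate for the composite. Its one calculation, 60 patients "with 80% power at the 5% significance level", concerns a 37% troponin reduction. It cannot be reproduced because no SD is given. Solving for the SD on the raw scale gives an implied coefficient of variation of 0.37 / [(1.960 + 0.842) × √(2/30)] = 0.51. This does not bear on the point; only the 30 per arm is carried forward.

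**Type I error if any of three readings at 0.05 counts.** For independent tests, 1 − 0.95³ = 14.3%, an upper reference. Cumulative readings are correlated. For cumulative rates p_i < p_j the large-sample correlation is √[p_i(1 − p_j) / (p_j(1 − p_i))]; for 10% and 20% this is √(0.08/0.18) = 0.67. Simulating 300,000 null trials per scenario, 30 per arm, gave:

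| Assumed rates: in hospital / 1 month / 6 months | Uncorrected chi-square | Fisher's exact |
|---|---|---|
| 10 / 20 / 30% | 11.5% | 4.6% |
| 10 / 15 / 25% | 11.3% | 4.1% |
| 15 / 20 / 30% | 10.3% | 4.8% |
| 20 / 30 / 40% | 10.3% | 5.5% |
| 30 / 35 / 40% | 8.6% | 4.8% |
| 20 / 22 / 25% | 7.9% | 4.0% |
| 5 / 10 / 20% | 10.4% | 3.0% |
| 10 / 30 / 50% | 12.8% | 5.4% |

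Three repeated log-rank-type looks gave 8.4-11.7% over the information fractions tried (10.7% at equal spacing). The 6-month chi-square alone gave 4.8-5.2%. One Cox or log-rank test over all follow-up is nominally 5%.

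**Observation window.** The window from randomisation is the stay in hospital, stay + 30 days at 1 month, and stay + 182 days at 6 months (stay counted from randomisation).

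| Assumed stays (days) | In hospital | 1 month | 6 months |
|---|---|---|---|
| 14 vs 21 | 21/14 = 1.50 | 51/44 = 1.16 | 203/196 = 1.04 |
| 10 vs 20 | 20/10 = 2.00 | 50/40 = 1.25 | 202/192 = 1.05 |
| 14 vs 28 | 28/14 = 2.00 | 58/44 = 1.32 | 210/196 = 1.07 |

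**What the window alone can do.** Suppose a constant daily event rate, equal in both arms, that gives 10% by day 14. By day 21 it gives 1 − 0.90^1.5 = 14.6%, so the in-hospital reading shows 10% against 14.6% with no treatment effect on the rate. At 6 months, a constant rate giving 30% by day 196 gives 1 − 0.70^(203/196) = 30.9% by day 203, which is a negligible gap.

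**The case against.** The strongest reply is that the article speaks of one primary endpoint, evaluated at three contacts, and names a time-to-event model in connection with it. Those contacts could simply supply data to one analysis, with error near 5% and unequal follow-up largely handled by censoring. A multiplicity rule may also stand in an analysis plan that is not shown. This stands against any unconditional error figure. It does not settle the matter, because the Cox model as worded assesses prognostic variables without treatment, and the time-to-event comparisons between arms are given to other outcomes. The time at which a primary endpoint is read is part of its definition.

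A reader might infer more than the documents support:

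- **That type I error is 10% or more.** No passage says that each time is tested separately or that one success suffices. With few events, uncorrected chi-square is also doubtful: a 10% rate means 3 expected events per arm. Fisher's test, which the article does not name, would keep the error near or below 5%.
- **That RIC is expected to shorten stay.** The article only makes duration an endpoint for judging RIC; it predicts no direction.
- **That patients who die in hospital, having no discharge date, damage the primary endpoint.** Death from any cause is a component, so they have already reached it.
- **That Table 1 contradicts the follow-up text.** NICU discharge is a data-collection row, and the later rows match the text. What remains is an ambiguity over whether discharge means leaving the NICU or the hospital.

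**Conclusion.** The point holds as a defect in how the endpoint is fixed. No reading or single analysis is primary, and the window for each reading hangs on a post-randomisation event that treatment may affect.

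Its effect on type I error is conditional: about 8-13% for three uncorrected chi-square tests with any success counting, about 3-5.5% for three Fisher tests, and about 5% for one analysis, all at 30 per arm under assumed event rates. The unequal window matters most for the in-hospital reading, less at 1 month, and little at 6 months: 50%, 16% and about 4% for assumed stays of 14 and 21 days. The direction and size of any real difference in stay are unknown.

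**What to change.** - Name one primary analysis: time from randomisation to first composite event, compared between arms and censored at the same fixed day in both, for example day 180.
- Report in-hospital and 30-day estimates as descriptive.
- State whether discharge means leaving the NICU or the hospital.
- Time visits from randomisation for patients not yet followed.

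This needs no extra patients or visits. For patients already followed, recorded event dates allow the composite to be re-anchored. A completed 6-month visit falls at stay + about 182 days, so it already covers day 180.

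The cost lies in the other measures. With stays of 14-21 days, a 1-month visit falls at days 44-51, which is 14-21 days after a day-30 target. mRS, GOS, echocardiography and biomarkers measured at such visits cannot be re-timed. They should be kept and analysed with their actual day from randomisation, accepting a mixture of visit timings.

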### Secondary Endpoints

The secondary endpoints are death from any cause, a composite of major adverse cardiac and cerebrovascular events, serum cardiac biomarker cTnI, NT-pro BNP, modified Rankin Scale (mRS) score, Glasgow Outcome Score (GOS), cardiac function determined by echocardiography, ECG changes (QT interval and possible ST elevation), and blood uric acid level measured prior to RIC treatment, at discharge from the NICU, and at the 1- and 6-month follow-up. The average hospitalization duration will be recorded as a secondary endpoint to evaluate the efficiency of RIC.

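### The trial is sized on serial troponin, but the listed troponin endpoint leaves out the 48-hourly samples, the 37% reduction has no time point or scale, and no stated troponin comparison uses baseline or the repeated measures

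*Protocol article*

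**What the plan says.** All references are to the Protocol article.

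- **Sample Size.** The power calculation is "based on serial troponin measurements, taken as continuous outcome variables". The target is given as "we hypothesized a troponin level reduction of 37% with 80% power at the 5% significance level", leading to 60 patients, 30 per arm. The supporting figures are a 40% fall in a ten-patient pilot and an 18–62% range from earlier RIC studies. No SD, scale or time point is attached to any of them.
- **Intervention and Follow-Up, with Table 1.** RIC runs for five days. Blood is taken before RIC and then every 48 h after it until the patient leaves the NICU, and again 1 and 6 months after discharge. For controls, "blood samples will be collected at the same time points as those in the RIC group".
- **Secondary Endpoints.** cTnI stands in a list that ends "measured prior to RIC treatment, at discharge from the NICU, and at the 1- and 6-month follow-up". The 48-hourly samples are not mentioned. Average hospital stay is also a secondary endpoint.
- **Data Management and Statistical Analysis.** "In univariate analyses, patient- and clinical-related factors will be compared" by chi-square, ANOVA, t-test or Mann–Whitney as appropriate. Baseline cardiac biomarkers are candidate variables for an initial model, but multivariable modelling is named only for the primary endpoint, mRS and GOS.

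**The concern.** The number of patients is justified by one variable, troponin measured serially. When that variable appears as an endpoint, the serial samples have gone and three kinds of post-treatment value remain: NICU discharge, 1 month and 6 months.

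NICU discharge happens after randomisation, at a time set by each patient's course. The protocol treats length of stay as something RIC may change. If stays differ between arms, a discharge value compares the arms at different elapsed times and mixes treatment effect with time. The 1- and 6-month visits are counted from discharge, so they shift in the same way.

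The 37% itself cannot be tied to any of these values. It has no stated time, and a percentage reduction is naturally a ratio (0.63), yet no log scale or ratio measure is given. Finally, every patient has a pre-RIC troponin and usually several later ones, but no stated troponin comparison uses either. What is at stake is whether the comparison eventually run is the one for which 60 patients were judged enough, and whether precision already paid for is used.

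**Working it through.** **1. Do the passages agree on when troponin is measured?**

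| Section | Troponin times |
|---|---|
| Sample Size | Serial; no times given |
| Intervention and Follow-Up, Table 1 | Before RIC, every 48 h until NICU discharge, at NICU discharge, 1 and 6 months |
| Secondary Endpoints (natural reading) | Before RIC, NICU discharge, 1 and 6 months |

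The data for a serial endpoint will be collected. The mismatch is in the endpoint definition.

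**2. Can N = 60 be reproduced?** Inputs from Sample Size: 37% reduction, 80% power, 5% significance, 30 per arm. Two-sided testing is assumed. No SD is given, so the figure can be neither confirmed nor refuted, and I solved backwards.

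- Standardised difference needed: normal approximation, (1.960 + 0.842) × √(2/30) = 0.723; t-test, 0.736.
- Log scale: −ln(0.63) = 0.462. Implied log-SD = 0.462/0.736 = 0.63 (0.64 with the normal approximation).
- Raw scale: implied SD = 0.37/0.736 = 0.50 of the control mean (0.51 with the normal approximation).

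So 60 patients fit a 37% reduction only if the log-SD is about 0.63. The protocol does not state this.

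**3. What would baseline adjustment add?** With correlation ρ between log baseline and log follow-up troponin, ANCOVA multiplies the residual variance by 1 − ρ², so the standardised difference becomes 0.462 / (SD × √(1 − ρ²)). Neither ρ nor the SD is in the documents; both are assumed. Power is for a two-sided t-test with 30 per arm and one post-treatment value.

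| ρ | 1 − ρ² | Power, log-SD 0.63 | Power, log-SD 1.0 |
|---|---|---|---|
| 0 (unadjusted) | 1.00 | 80% | 42% |
| 0.3 | 0.91 | 84% | 45% |
| 0.5 | 0.75 | 90% | 53% |
| 0.7 | 0.51 | 98% | 69% |

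As equivalent sample size, 1/(1 − ρ²) is 1.10, 1.33 and 1.96.

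**4. Does the time point matter?** Keep the back-solved log-SD and the unadjusted test with 30 per arm, and suppose the effect at the analysed time is smaller than 37%.

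| Reduction at the analysed time | −ln(1 − reduction) | Power |
|---|---|---|
| 37% | 0.462 | 80% |
| 30% | 0.357 | 58% |
| 25% | 0.288 | 41% |
| 18% (low end of the protocol's cited range) | 0.198 | 22% |

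The documents do not say how the effect changes over time. The table shows only why the time belonging to the 37% must be stated.

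**The case against.** **The timing clause may not govern troponin.** It closes a list that includes death, which cannot be measured before RIC, so it cannot apply literally to every item and might attach to uric acid alone. Troponin timing would then come from the sampling schedule, which includes the 48-hourly draws. The ambiguity is real, but that reading leaves the powered variable with no endpoint time at all. Either way the text needs correcting.

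**A reader might infer that the plan mistimes an acute 37% effect.** The documents do not support that. The protocol never calls the 37% acute and gives it no time. The five-day course and the Introduction's description of transient dysfunction make an early effect plausible, but that is inference. The supported statement is that the time is missing.

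**A reader might also infer that the plan commits to unadjusted two-sample tests of troponin.** It does not say so. The sentence naming those tests concerns patient and clinical factors and stands beside the covariate screening for the Cox models. The Introduction promises an exploration of changes in biomarkers, which implies some use of baseline, and an unseen analysis plan may supply a model. What stands is narrower: t-test, ANOVA and Mann–Whitney are the only between-group methods named that suit a continuous outcome, and the modelling named is for other outcomes. Nor does the article fix a scale contrary to the log scale, since the Mann–Whitney result is unchanged by taking logs.

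**The sampling clock in controls.** It would be too strong to say controls have none, because they are sampled at the same times as the RIC arm. It is unclear only whether 48-hourly sampling runs from the first session or from the end of the five-day course, and how that is anchored in a control. The promised manual may settle this.

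**Conclusion.** The point holds as a mismatch between passages and an avoidable loss of precision. It does not show that the troponin analysis is wrong. Three things rest on the text alone: the serial basis of the sample size is missing from the endpoint list on its natural reading, the 37% has no time point or scale, and no stated troponin comparison uses baseline or the repeated measures. That discharge timing could bias the comparison follows from discharge being a post-randomisation time together with the protocol's own interest in length of stay. Whether stays will differ is unknown.

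The power figures are illustrations. They assume a two-sided t-test, 30 per arm, a log-SD of either 0.63 (back-solved so that N = 60 works) or 1.0, and ρ between 0.3 and 0.7. The gain is about 4 to 18 percentage points at the smaller SD and 3 to 27 at the larger. At weak correlation it is modest. This should be changed because troponin is the only variable the sample size was built on.

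**What to change.** 1. In Sample Size, state the time window and scale to which the 37% applies, and the SD used.
2. In Secondary Endpoints, define the troponin endpoint as log cTnI over the existing 48-hourly NICU samples, with one clock for both arms, for example from randomisation. Match the nominal times to the actual sampling schedule, since a fixed grid from randomisation need not coincide with sampling every 48 h after RIC. Make clear which endpoints the timing clause covers.
3. In the analysis section, name a mixed model with arm, time, arm-by-time and log pre-RIC cTnI, or ANCOVA on a serial summary such as log AUC with the same covariate. Report the geometric mean ratio with its confidence interval against the planned 0.63.
4. Keep the NICU-discharge and 1- and 6-month values as supportive.

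**Cost.** Mainly wording. If the clock follows the actual schedule, no extra patients or samples are needed. The downside is small: sampling stops at NICU discharge, so later values will be missing in a way linked to clinical course. The mixed model handles this only under missing at random, so add a simple sensitivity analysis.

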### Sample Size

No previous studies have focused on utilizing RIC to prevent TTS in patients after acute stroke. Most existing evidence utilized troponin I assay for the detection of cardiac injury. Power calculations for this proof-of-concept study will be based on serial troponin measurements, taken as continuous outcome variables with a predicted difference. Previous studies on RIC indicated a cardioprotective effect of RIC in reducing troponin levels by 18–62% (45–48). Based on the results of a pilot study in our center (the troponin level decreased by 40%, *n* = 10), we hypothesized a troponin level reduction of 37% with 80% power at the 5% significance level, and we calculated a sample size of 60 patients (*n* = 30 in each arm of the study).

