## Discussion

We described the design and methods of a single-center, two-arm, parallel-group, randomized controlled trial investigating the efficacy of RIC in patients with TTS after acute stroke. This is the first RCT to address important questions about the heart protection effect of RIC in this population with such rigorous methodological design. It is expected that the study findings might hopefully become part of local protocols or international guidelines, allowing patients and care providers to make informed decisions and provide comprehensive information for future study designs.

A limitation of this study is that it involves only one center and a minority of the subjects with TTS. This might influence the generalizability of the research results. Another limitation of this study is the non-blinding of the physician responsible for performing RIC. To reduce potential influence of this limitation on the outcomes, the physicians have no further role in the clinical trial and the staff responsible for data collection and analysis will be blinded.

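### The 80% power is for troponin, a secondary endpoint; the trial is not sized for its primary composite, for which no control rate, effect or power is given

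*Protocol article*

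**What the plan says.** Three sections of the protocol article bear on this.

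- **Primary Endpoints:** "The primary endpoint is a composite of death from any cause and major adverse cardiac and cerebrovascular events". The components are recurrent Takotsubo syndrome, myocardial infarction, stroke or transient ischemic attack, and death, assessed in hospital and at 1 and 6 months.
- **Secondary Endpoints:** the list includes "serum cardiac biomarker cTnI, NT-pro BNP", so troponin is secondary.
- **Sample Size:** "Power calculations for this proof-of-concept study will be based on serial troponin measurements, taken as continuous outcome variables with a predicted difference". Then: "we hypothesized a troponin level reduction of 37% with 80% power at the 5% significance level", from which "we calculated a sample size of 60 patients", that is "30 in each arm of the study". The support offered is a range of 18–62% troponin reduction in earlier studies and a 40% decrease in a pilot of 10 patients.

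Data Management and Statistical Analysis sets significance at p < 0.05 and names Cox regression for the primary endpoint. The limitations in the Discussion are the single centre, the small number of Takotsubo subjects (linked to generalizability) and the unblinded treating physician. Power is not among them.

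**The concern.** A sample-size statement tells the reader what the main test can detect. Here it describes a different variable, of a different type (continuous rather than an event), with a lower rank in the endpoint hierarchy. The article does not leave the justification of N to another document. It gives one, and that one does not apply to the endpoint named primary.

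What is at stake is how the headline result is read. If the composite shows no significant difference, a reader who sees 80% power may conclude that remote ischemic conditioning does not work, when the comparison had little chance of showing a moderate clinical benefit. The stated aim of a proof-of-concept study, whether cardiac injury is reduced (Objectives), would meanwhile be answered only by a secondary endpoint.

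**Working it through.** **Step 1. The protocol's own figure.** Inputs from Sample Size: 37% reduction, 80% power, 5% level (two-sided assumed), 30 per arm. No SD is stated, so N = 60 can be neither confirmed nor refuted. Solving backwards for the standardized difference:

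d = (1.96 + 0.84) × √(2/30) = 0.72 (0.74 with the t-test).

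For a single measurement per patient this implies a raw SD of 0.37/0.72 ≈ 0.51 of the control mean, or a log-scale SD of −ln(0.63)/0.72 ≈ 0.64. The figure is attainable for troponin. It says nothing about the composite.

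**Step 2. Power for the composite.** Inputs: 30 per arm and two-sided 5%. Two further inputs are assumptions, because the protocol gives neither: the control risk p₁, varied over a wide range, and a risk ratio of 0.63, which carries the troponin percentage over to clinical events. With p₂ = 0.63 p₁ and p̄ = (p₁ + p₂)/2:

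power ≈ Φ{ [ (p₁ − p₂)√30 − 1.96 √(2p̄(1 − p̄)) ] / √(p₁(1 − p₁) + p₂(1 − p₂)) }

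Example at p₁ = 0.30: p₂ = 0.189 and p̄ = 0.2445. The numerator is 0.111 × 5.477 − 1.96 × 0.608 = −0.583 and the denominator is 0.603. Φ(−0.97) ≈ 0.167.

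| Assumed control risk | Treated risk at RR 0.63 | Power, formula | Chi-square, exact enumeration | Fisher, exact enumeration |
|---|---|---|---|---|
| 10% | 6.3% | 7.5% | 8.0% | 1.4% |
| 20% | 12.6% | 11.7% | 12.1% | 5.8% |
| 30% | 18.9% | 16.7% | 16.6% | 10.6% |
| 40% | 25.2% | 22.8% | 22.5% | 15.6% |
| 52% | 32.8% | 32.2% | 32.7% | 23.8% |
| 70% | 44.1% | 52.7% | 53.5% | 43.0% |
| 87% | 54.8% | 79.9% | 81.0% | – |

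Exact enumeration sums the probabilities of all pairs of event counts (0–30 in each arm) for which the test gives p < 0.05.

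**Step 3. Numbers needed.** Under the same assumptions, 80% power takes 390 patients per arm at a 20% control risk, 235 at 30%, 157 at 40% and 103 at 52%.

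**Step 4. Time-to-event check.** Cox regression is named for the primary endpoint, so the hazard scale is also relevant. Under proportional hazards a risk ratio of 0.63 corresponds to HR = ln(1 − 0.63p₁)/ln(1 − p₁), which is 0.60 at p₁ = 20% and 0.54 at p₁ = 52%. Schoenfeld's formula, events = 4 × (1.96 + 0.84)²/(ln HR)², then asks for about 123 and 83 events. Both exceed the 60 patients enrolled. The power from the events expected with 30 per arm is about 12% and 34%, in line with the table.

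**The case against.** The strongest defence is openness. Sample Size says plainly that the calculation rests on troponin, and the trial is called proof-of-concept in the abstract, the Objectives and Sample Size. That stands: nothing is concealed, and the text does not claim 80% power for the composite. But openness does not supply a justification for the primary comparison, and nowhere is the reader told that this comparison is underpowered.

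Several stronger readings are tempting, and the documents do not support them.

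- **A fixed power figure for this trial, such as 12–33%.** It depends on an assumed control risk of 20–52%. The 52% in the Introduction counts complications such as heart failure, pulmonary edema and shock, which are not components of the composite.
- **That the protocol hypothesizes a 37% clinical benefit.** It hypothesizes only a troponin reduction. The risk ratio of 0.63 is an assumption of this check.
- **That 80% power for troponin fails unless the log-scale SD is at most about 0.63.** That limit is for one measurement per patient. The protocol takes a pre-treatment sample and repeats it every 48 h; baseline adjustment with an assumed correlation of 0.5–0.7 raises the tolerable SD to about 0.73–0.88. The unstated SD may be in a fuller document and is not a finding.
- **That significance would require an implausibly large effect.** This confuses the true effect needed for 80% power with the observed difference needed for p < 0.05. By chi-square, 16/30 versus 8/30 gives p = 0.035 and 12/30 versus 5/30 gives p = 0.045.
- **That the hope of reaching guidelines ("It is expected that the study findings might hopefully become part of local protocols or international guidelines") is an error.** It is cautiously worded, and objecting to it is a matter of preference.

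**Conclusion.** The point holds as a mismatch that can be read directly from the protocol: the sample size and the 80% power belong to a secondary biomarker, and the primary composite has no stated control rate, effect or power. No assumption is needed for that.

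The size of the shortfall is conditional. It assumes a risk ratio of 0.63, a two-sided 5% test, 30 per arm and no dropout. On those terms power runs from about 8% at a 10% control risk to about 53% at 70%, and reaches 80% only near 87%. A larger true clinical effect would raise these figures and a smaller one would lower them. Over this range of control risks, a non-significant result on the composite would not be evidence that the intervention is ineffective. This does not show that N = 60 is wrong for troponin; the document does not allow that to be judged.

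**What to change.** Amend the protocol and the registry entry before any unblinded look at data, in one of two ways.

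1. **Preferred.** Make cTnI over the acute phase the single primary endpoint, analysed on the log scale with baseline adjustment, using the serial samples already collected. Move the composite to a secondary endpoint, reported with an effect estimate and 95% CI and without an efficacy claim. The primary endpoint then matches both the sample-size basis and the proof-of-concept aim.
2. **If the composite stays primary.** State in Sample Size that the trial is not powered for it and that the 80% refers to troponin. Add its power or detectable effect over a range of assumed control rates, as in the table above.

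Neither route needs more patients, samples or visits. The cost is in what can be claimed: under the first, the headline conclusion is limited to a biomarker; under the second, the stated power for the primary endpoint becomes much less favourable.
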